#### Anthropometry

Body height and weight measurements will be taken using a weight and height scale (JT-918C, J-SKY company, China), under conditions when the subject is wearing only light clothing/underwear. Waist circumference will be measured at the midpoint between the lowest point of the lowest rib and the highest point of the ilium. Hip circumference will be measured at the greater trochanter of the femur. The hip and waist circumferences were averaged by repeating the measurements twice. In the event of a difference of ?3 cm between the two measurements, a third measurement will be taken and the average of the two closest measurements will be used. Body composition (fat mass and skin mass) will be measured using a body composition analyzer (S-ONE, JingHai Health, China).

#### Blood samples

Fasting venous blood samples will be collected via an anterior elbow vein catheter on the four test days (V1-V4) before and after the two intervention periods. Blood samples will be immediately centrifuged for 15 min (3,000 g at 4°C), frozen at −20°C, and analyzed within 30 days of collection. The analysis will include assessment of fasting glucose, fasting insulin, HbA1c, and C-peptide levels. Plasma glucose will be measured by the glucose oxidase technique. Insulin and C-peptide measurements will be performed by electrochemiluminescence.

#### Subjective appetite

The VAS will be used to investigate subjective satiety, hunger, and desire for the next meal (32). After the introduction of the snacks, subjective appetite will be assessed using the VAS at time points of 10 and 20 min. Participants will rate each of the following 4 questions by marking vertically on a 10 cm horizontal line with descriptive anchors on either side (“not at all” to “extremely”): [1] How full do you feel? [2] How hungry do you feel? [3] How strong is your desire to have the next meal? and [4] How much do you think you could (or would you want to) eat right now?

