**Questionnaires**					
Sociodemographic characteristics	X				
Eating habits	X				
Acceptability and compliance					X

a *CGM between 8:00 and 9:00 at Visit 1*;

b *collect CGM data from Visit 1 to Visit 4 for 14 consecutive days*;

c *at time points of 10 and 20 min after consumption of the snacks*;

d *records during the entire study*.

*CGM, continuous glucose monitoring; VAS: visual analog scale*.

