#### Secondary outcomes

Secondary outcomes consist of various metabolic and behavioral indicators, including changes in insulin, C-peptide, fasting blood glucose (FBG), HOMA-IR, HOMA-β, subjective appetite, satiety, hunger evaluated by the VAS, body height, and weight measurements.

We will assess changes in these outcomes in two different experimental periods: [1] from baseline to the end of the first intervention period (D3-D6) and [2] from the end of the run-in period to the end of the second intervention period (D10-D13). The acceptability and maintainability of the intervention will also be assessed after the completion of the interventions (D14).

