Furthermore, we will control for confounding factors as strictly as possible. This protocol is based on past studies of the effects of different intervention time points, intervention foods, intervention energies, and intervention populations. However, this study is extended by physical activity level monitoring and daily nutritional recordings (electronic food diary, CGM, and activity records) through timely supervision of the subjects by the researchers and hunger, satiety, and blood glucose and insulin resistance indices will be measured before and after energy intake. During both the ad libitum and standard meal periods, subjects will be asked to record whether and how much food is left over from each meal to assess the effect of the intervention on energy intake at regular meals and to exclude changes in GV due to differences in energy intake. To exclude the influences of different dietary patterns, researchers will train the subjects to eat in the same fixed meal order and have the same duration of each meal (chewing pace) to control for confounding factors in the 3-day balanced meal run-in period. At the end of the experiment, subjects will also be surveyed about their perceptions of the intervention to obtain information about its acceptability, compliance, and adherence. Compared to previous studies, these tools and measures will help avoid confounding factors, advance the understanding of the effect of the premeal snacking intervention on GV and promote the application of the intervention to a wide range of the population. Moreover, we will also administer 250 ml of water to the control group, similar to the 3 intervention groups, to avoid the influences of stomach capacity and swallowing behavior changes on the results (44, 45). In addition, for data processing, we will exclude data from the first day of each phase and the last day of wearing the CGM to exclude data differences caused by the instability of CGM devices.

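### Appetite, hunger and satiety are defined as changes, but the only ratings described are 10 and 20 minutes after the snack, so the change has no starting value

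*Protocol article*

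**What the plan says.** All references are to the protocol article.

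- **Secondary outcomes.** The list is introduced as "including changes in insulin, C-peptide, fasting blood glucose (FBG), HOMA-IR, HOMA-β, subjective appetite, satiety, hunger evaluated by the VAS". The same section fixes two windows for change: baseline to the end of the first intervention period, and the end of the run-in to the end of the second.
- **Statistical analysis plan.** Within-group change is the post-intervention value minus the pre-intervention value, with paired t-tests when the assumptions hold.
- **Subjective appetite.** Once the snack has been given, "subjective appetite will be assessed using the VAS at time points of 10 and 20 min". Four questions are each marked on a 10 cm line.
- **Table 2, footnote c.** The VAS is taken "at time points of 10 and 20 min after consumption of the snacks".
- **Test snacks.** The snack is given 30 minutes before lunch; controls receive water.
- **Standard balanced meals run-in period.** No pre-meal snacks are given on D7 to D9.
- **Continuous glucose monitoring.** D2 and D9 supply the baseline glucose values for the two periods.
- **Discussion.** "hunger, satiety, and blood glucose and insulin resistance indices will be measured before and after energy intake".

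**The concern.** A change needs a starting value. The outcome definition and the analysis section both call for one, yet the two places that give VAS times list only times after the snack. If the trial runs as written, the paired pre/post test cannot be carried out for appetite, hunger and satiety, although all three are named in the secondary objective. The analysts would have to replace the stated outcome with a post-snack comparison after the fact. Pre-lunch hunger can be expected to differ between people, and with 8 participants per arm a post-only comparison carries all of that variation. A rating not taken before the snack cannot be recovered later.

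**Working it through.** No figure in the plan underlies this point, so there is none to reproduce. The check sets the passages side by side and then sizes the gain from a pre-snack rating.

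**1. Ratings on the snack-to-lunch clock.** Put the snack at 0 minutes and lunch at +30 (Test snacks). The ratings fall at +10 and +20 (Subjective appetite; Table 2, footnote c), which is 30 − 10 = 20 and 30 − 20 = 10 minutes before lunch.

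| Meaning of energy intake in the Discussion | Ratings before | Ratings after |
|---|---|---|
| The snack (0 min) | 0 of 2 | 2 of 2 |
| Lunch (+30 min) | 2 of 2 | 0 of 2 |

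Neither meaning gives a before-and-after pair.

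**2. Starting value for the period-level change.**
- Period 1 runs from D3 to D6. D2 is the pre-intervention baseline day and has no snack.
- Period 2 runs from D10 to D13. D9 is the last run-in day, and snacks are withheld from D7 to D9.
- Both rating times are counted from the snack. On D2 and D9 there is no snack to count from, and no other VAS occasion is described for those days.
- Taking D2 and D9 as the VAS baseline days is an inference from their use for glucose. The article names no separate VAS baseline day.

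The stated change therefore lacks its starting value within a day and across a period.

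**3. What a 0-minute rating alone would supply.** It gives a within-day baseline on snack days. It does not give the value at period baseline or at the end of run-in, so it does not by itself make the outcome computable as now defined. The definition must change too, or D2 and D9 ratings must be added.

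**4. Precision.** The article gives no VAS standard deviation and no correlation between pre- and post-snack ratings. Let r be that correlation; r = 0.5 to 0.7 is an assumption. With equal variances before and after, and relative to comparing post-snack ratings alone (variance factor 1):

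| r | Covariate adjustment, 1 − r² | Reduction | Simple change from 0 minutes, 2(1 − r) |
|---|---|---|---|
| 0.5 | 1 − 0.25 = 0.75 | 25% | 1.00 |
| 0.7 | 1 − 0.49 = 0.51 | 49% | 0.60 |

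The last column shows why the 0-minute value is better used as a covariate than subtracted: at r = 0.5 subtraction gains nothing over the post-snack rating. The covariate costs one residual degree of freedom, from 32 − 4 = 28 to 27 with full retention.

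**The case against.** **The outcome is a change across a period, not across one snack.** This is correct, and a complaint about the missing pre-snack rating alone would miss the definition. It does not rescue the plan, because no rating is described at the start of either period.

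**The Discussion sentence is loose.** It places hunger and satiety alongside insulin resistance indices, yet blood is drawn fasting at V1 to V4, so it cannot be literal for the whole list. It may simply mean before and after the intervention. A reader might infer that it promises a pre-snack VAS; the wording is too loose for that. The mismatch between the outcome definition and the rating times stands without it.

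**The article condenses a fuller protocol.** A 0-minute rating may exist there. But this article states the times explicitly in two places and defines an outcome those times cannot produce, which goes beyond an omitted detail.

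**Table 2 may hold the answer.** The single VAS mark appears under V0. Physical activity and sleep records also show one mark there, although the text has them recorded throughout, so alignment or merged cells were probably lost. A reader might call the V0 mark an error; the text available cannot support that. Nor can a V0 mark supply the baseline: its footnote ties it to snack consumption, and randomisation follows screening.

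**The randomised comparison is still valid.** This stands. A reader might infer that the appetite results would be biased, but nothing supports that: post-snack ratings can be compared between arms with the planned ANOVA and Dunnett's test.

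**The precision gain is assumed.** This also stands. A reader might turn the variance reduction into an equivalent number of participants per arm. The article's sample size rests on MAGE and none on the VAS, so such a figure would suggest a power target that does not exist.

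**Conclusion.** The point holds as a modest defect in a named secondary outcome. As written, the change in appetite, hunger and satiety has no starting value, so neither that change nor its paired test can be produced. The post-snack comparison between arms remains unbiased, and MAGE and the other glucose outcomes are unaffected. The conclusion rests on the rating times stated in the text and footnote, and does not depend on the alignment of Table 2. The 25% to 49% reduction in residual variance is conditional on the assumed correlation of 0.5 to 0.7 and describes precision only; the mismatch stands whatever the correlation.

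**What to change.** 1. Add a 0-minute rating on the same four 10 cm lines, immediately before the snack or water, in all four arms on every VAS day.
2. In Secondary outcomes, redefine the VAS outcome as the 10- and 20-minute ratings compared between arms, with the 0-minute rating as covariate.
3. If the change across each period is to be kept, also take pre-lunch ratings at matched clock times on D2 and D9. Step 1 does not replace these.
4. Bring Secondary outcomes, Subjective appetite, Table 2 footnote c and the Discussion sentence into agreement.

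The cost of step 1 is four extra marks per rating day and a short amendment, with no extra visit. Step 3, if chosen, adds four marks for each matched time on two days: 4 × 3 = 12 marks per day if all three times are matched.

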#### Interviews

Face-to-face interviews will be conducted at V4 to evaluate the participants' experiences and perceptions of the intervention in depth. All subjects will be invited to a personal semistructured interview of ~20 min to explore the feasibility and acceptability of the premeal snack intervention being included in their daily dietary habits. It will help to understand the feasibility of the intervention and the acceptability and sustainability of integrating this intervention into their daily lives. If subjects withdraw from this trial, they will be invited to record their reasons for withdrawing and their perceptions of the interventions by a face-to-face interview.

### Comparisons

First, the three intervention arms will be combined as a group and compared with the control group to evaluate whether the premeal intervention could improve GV. Second, the two arms with high-protein snacks will be combined as a group and compared with the control group; moreover, the high-fat snack arm will be compared with the control group to evaluate whether the two snacks (high-protein and high-fat snacks) could improve GV. If both the high-protein and high-fat snacks show significant improvement effects, we will further directly compare the high-protein snack (combining milk powder and soy powder into one group) with the high-fat snack (almonds) interventions to evaluate which is better. Third, we will also compare the milk powder group with the control group and the soy powder group with the control group, and if both high-protein snack groups show significant improvement, we will further compare the animal protein and plant protein groups directly to verify whether the plant protein group is similar to the animal protein group. Finally, we will compare all the results from different dietary patterns to determine whether premeal snacks have similar effects under habitual diet and standard balanced meals.

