In studies of the second meal effect, the meal pattern is also very important to the results. Most of the currently proposed premeal intervention studies are conducted under well-controlled laboratory conditions with uniformly balanced diets or use glucose tolerance tests to simulate eating behavior. Although the effects were obvious, it is not clear that similar benefits can be achieved under real daily diet conditions. Moreover, single nutrients or intervention foods in experimentally specific ratios are not readily available in daily life and are difficult to adapt to the different dietary habits of people in China and other regions, which may lead to poor adherence. Therefore, we will select easily accessible natural foods, i.e., soy powder, milk powder, and almonds, to represent high plant protein, high animal protein, and high fat premeal snacks intervention, respectively, and evaluated their effects on GV under two different dietary patterns: habitual diets and balanced standard meals. In this trial, we will fully consider dietary habits, offer common foods as premeal snacks without energy restrictions, and detect the effects on GV and energy intake. Our trial is expected to have high applicability, operability, and acceptability, which can provide evidence for further application in T2DM populations.

The primary aim of this study is to evaluate whether premeal snacks of natural foods improve GV and which kind of premeal snacks lead to better effects in prediabetic subjects. We hypothesize that plant-based high-protein snacks will lead to a non-inferiority effect of animal-based high-protein snacks on GV. The secondary objective is to evaluate whether these interventions have a positive effect on insulin, HOMA-IR (homeostasis model assessment for insulin resistance), HOMA-β (homeostasis model assessment for β cell function), C-peptide, body weight, waist circumference, abdominal circumference, subjective appetite, hunger, and satiety. Furthermore, we will assess the acceptability and maintainability of these interventions.

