### Statistical methods

#### Sample size determination

The mean amplitude of glycemic excursions (MAGE) was chosen as the primary outcome indicator and it is expected that the MAGE will be reduced by 20% based on a study by Imai (33). Using PASS software (version 11.0), a sample size of 6 participants per group is required using the non-inferiority test for comparison of sample means. Assuming a 20% dropout rate, the sample size required for this study is 8 participants for each group.

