#### Statistical analysis plan

All parameters will be assessed for normality using the Kolmogorov-Smirnov test, and homogeneity of variance will be tested using the Levene test. Descriptive statistics will be expressed as the mean ± standard deviation (SD) for normally distributed data and as the median (Q1-Q3) for non-normally distributed data. Mean changes in parameters within the group will be assessed by calculating the difference between pre and postintervention measurements. When the data are normal and the variance is equal, paired *t*-tests will be used to assess the effect of interventions. Differences between groups will be assessed using the variance ANOVA test. Dunnett's test will be used to determine whether there is a significant difference between the experimental and control groups. When the assumptions for parametric tests are not met in the data, non-parametric statistical methods will be used.

Subgroup analyses by sex will be performed to explore whether the effect is modified by sex. The correlations between physiological factors and blood glucose levels will be assessed by Pearson's or Spearman's correlation analysis. Some *post-hoc* exploratory analyses will also be conducted. All analyses will be performed using SPSS version 24.0 (SPSS Inc. Chicago, IL, USA). The criterion for statistical significance will be a two-tailed *p* < 0.05.

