## Discussion

This is the first trial that directly assess the effects of three types of natural snacks on GV. One of the primary aims of this study is to determine which type of snacks is better for GV improvement. Short-term and long-term studies showed that high-protein and high-fat snack interventions could improve glucose metabolism, β cell function, lipid profile, satiety, and body weight, etc. (34–38), while previous experiments also reported that high-protein snacks were better at reducing hunger, bringing satiety, and reducing energy intake for the next meal (39). We hypothesize that all three types of snacks could improve GV and perhaps high-protein snacks have a better effect. In addition, most previous studies focused on separate animal-based protein and suggested that premeal animal protein has a superior effect on glycemic control, probably because of the high branched-chain amino acid content of whey protein, which allows for faster digestion and absorption of milk, causing a significant postprandial amino acid response and rapid first-phase insulin release (40, 41). However, none of these studies assessed the effect of plant-based and animal-based high-protein natural snacks on GV. In this trial, we will directly compare the effects of these two types of high-protein snacks and expect to observe a non-inferiority effect of soy powder compared to milk powder. We also hypothesize a non-inferiority effect of plant-based high-protein snacks (whole soy powder) compared with animal-based high-protein snacks (milk powder) on GV improvement. If this hypothesis is proven, the effective use of soy powder could also provide more options for the lactose-intolerant population.

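### Soy is hypothesised non-inferior to milk, but the stated analysis holds only two-sided difference tests, which cannot show non-inferiority or similarity

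*Protocol article*

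**What the plan says.** Four parts of the protocol article bear on the soy-milk question.

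- **Hypothesis.** The Introduction states: "We hypothesize that plant-based high-protein snacks will lead to a non-inferiority effect of animal-based high-protein snacks on GV". The Discussion repeats that the authors "expect to observe a non-inferiority effect of soy powder compared to milk powder".
- **Sample size.** Sample size determination says that "a sample size of 6 participants per group is required using the non-inferiority test for comparison of sample means". The only effect figure there is an expectation: "it is expected that the MAGE will be reduced by 20" percent. It is not called a margin.
- **Decision step.** Comparisons first sets soy and milk each against control. Then, "if both high-protein snack groups show significant improvement", it plans to "compare the animal protein and plant protein groups directly to verify whether the plant protein group is similar to the animal protein group". No criterion for similarity is attached.
- **Analysis.** The Statistical analysis plan section lists paired t-tests within groups, ANOVA between groups, Dunnett's test against control, and non-parametric substitutes. It closes with one criterion for the trial: "The criterion for statistical significance will be a two-tailed" p < 0.05.

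**The concern.** The hypothesis and the sample size belong to a non-inferiority framework; the stated tests belong to a difference framework. Dunnett's test compares each snack with control and leaves soy versus milk untouched. ANOVA, or its non-parametric counterpart, can only find a difference or fail to find one. If the stated methods are all that is applied, similarity can be concluded only from failure to find a difference. In arms of 6 to 8 people, that failure is common even when soy is materially worse.

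The Discussion attaches a practical message to the result: if the hypothesis is proven, soy powder becomes an option for people with lactose intolerance. The test as stated could not carry that message.

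**Working it through.** **1. The plan's own figures.** From 6 per group with 20% dropout: 6 / 0.8 = 7.5, rounded up to 8, and 4 x 8 = 32. This reproduces.

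The base figure of 6 cannot be reproduced, because the article gives no margin, SD, power or non-inferiority alpha. Solved backwards, with a true difference of zero assumed, margin/SD = sqrt(2/6) x (z for alpha + z for power):

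- one-sided 0.05, 80% power: 0.577 x (1.645 + 0.842) = 1.44
- one-sided 0.025, 90% power: 0.577 x (1.960 + 1.282) = 1.87

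With the t distribution the range is 1.54 to 2.08. If the 20% were the margin, the SD would have to be about 10% to 14% of mean MAGE (for example 0.20 / 1.44 = 13.9%).

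**2. The stated test taken alone (ungated).** Assumptions: two-sample t-test, two-sided 0.05, SD of the MAGE change = 1, soy truly worse by d. The non-centrality is d x sqrt(n/2) with 2n - 2 degrees of freedom. The 95% CI half-width is t(0.975) x sqrt(2/n).

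| n per arm | critical t | P(p >= 0.05), d = 0.5 | P(p >= 0.05), d = 1.0 | 95% CI half-width |
|---|---|---|---|---|
| 6 | 2.228 | 88% | 65% | 2.228 x 0.577 = 1.29 SD |
| 8 | 2.145 | 85% | 54% | 2.145 x 0.500 = 1.07 SD |

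Using the pooled error of all four arms changes little: at d = 1.0 the figures are 62% and 51%, with half-widths of 1.20 and 1.02 SD.

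**3. The test as gated.** Simulation with SD = 1, four arms, pooled error, a Dunnett gate for soy and for milk against control, then an unadjusted two-sided 0.05 soy-milk test. Soy is 1 SD worse than milk throughout. Joint means that the gate is passed and soy versus milk is non-significant; conditional means non-significant among trials that passed the gate.

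| Improvement over control, milk / soy (SD) | Joint, n = 6 | Joint, n = 8 | Conditional, n = 6 | Conditional, n = 8 |
|---|---|---|---|---|
| 1.5 / 0.5 | 5% | 6% | 83% | 77% |
| 2 / 1 | 18% | 22% | 78% | 68% |
| 3 / 2 | 54% | 49% | 66% | 53% |

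**4. What a margin-based rule could achieve.** If soy and milk are truly equal, the power to show non-inferiority at one-sided 0.025 is 12% (n = 6) or 15% (n = 8) for a margin of 0.5 SD, and 35% or 46% for 1.0 SD. For 80% power, a 0.5 SD margin needs 63 per arm and a 1.0 SD margin 16 per arm, before dropout.

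**The case against.** The strongest reply has three parts.

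First, a non-inferiority sample size needs a margin as input, so one was presumably entered. A condensed article may leave it to a fuller protocol or analysis plan that is not shown. This stands: the absence of a margin is not in itself an error. What remains is a conflict within the text, since the article's own analysis section sets a two-tailed difference criterion while its hypothesis and sample size are non-inferiority.

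Second, the gate. A reader might infer that the similarity claim becomes easier to reach the smaller and noisier the trial is, or that 54% and 65% are the chances of a false claim. Neither is supported. Small trials often fail the gate: in two of the three scenarios above the joint risk is lower at 6 per arm than at 8, and it can be as low as 5%. But the gate does not rescue the inference. Two arms can each beat control and still differ materially from each other.

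Third, a reader might infer that a non-significant p-value will be reported as similarity. The article does not say so. It only supplies no other means of verifying similarity, so the risk is that it may be read that way. Nor is soy versus milk the trial's whole purpose: it is the third and conditional comparison, although it is the hypothesis stated alongside the primary aim.

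**Conclusion.** The point holds as a mismatch between the stated hypothesis and sample-size basis (non-inferiority) and the stated analysis (two-sided difference tests). A non-significant soy-milk result would not support the hypothesis. With soy truly 1 SD worse, it occurs in 54% to 65% of trials for the ungated test and in about 53% to 83% of trials that pass the gate. The joint probability depends heavily on the true effects, from 5% to 54% in the scenarios tried.

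All these figures are in units of an assumed SD of the MAGE change, because the article gives none. The gated figures also assume a Dunnett gate and the listed effect sizes. The qualitative conclusion does not depend on those choices.

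**What to change.** Choose one of two routes, before allocation is unblinded.

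1. **Keep non-inferiority.** In Comparisons and in the Statistical analysis plan section, state the margin used in the sample-size calculation and justify it. Declare non-inferiority only if the upper limit of the two-sided 95% CI for soy minus milk in MAGE change (positive values meaning soy is worse) lies below that margin. Say openly that at 8 per arm this can succeed only with a margin of about 1 SD or more, or with an estimate that favours soy.
2. **Drop it.** Remove the non-inferiority and similarity wording from the Introduction, Comparisons and Discussion. Report the soy-milk difference with its 95% CI as exploratory, and state that a non-significant result is not evidence of similarity.

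The cost is wording and a less favourable soy claim. Neither route needs new participants or data. More participants would be needed only if the sponsor wanted adequate power for a tighter margin, as step 4 of the working shows.
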